### Composition of the data monitoring committee, its role and reporting structure {21a}

We do not have composition of the data monitoring committee.

### Adverse event reporting and harms {22}

Any adverse events that required additional pharmacological, interventional, or surgical management within 30 days after surgery will be collected and monitored. We regarded adverse events as postoperative complications and graded according to the Clavien-Dindo classification [23]. Adverse events will be treated according to the standards of care.

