### Objective {7}

This study aimed to evaluate the safety and efficacy of absorbable barbed sutures for midline fascia closure in minimally invasive surgery for colorectal and gastric cancers in comparison with conventional absorbable monofilament sutures.

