### Study design {8}

The Barbed trial is a prospective, superiority, single-center, randomized trial comparing the clinical outcomes of absorbable barbed sutures and monofilament sutures. A total of 312 patients will be enrolled and randomly allocated to use absorbable barbed or monofilament sutures for midline fascia closure in a 1:1 ratio. The surgical procedure used to close the midline fascia was standardized for both types of suture material. The investigator will examine the patients until discharge and at 6, 12, 18, 24, and 36 months postoperatively (Fig. 1). This study is ongoing at Jeonbuk National University Hospital and will last 3 years for each patient. This trial was registered with the Clinical Research Information Service of Korea.

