#### Secondary outcomes

Postoperative complications, including surgical site infection (SSI), pain, and quality of life, will be compared between the absorbable barbed suture and conventional absorbable suture groups.

Postoperative complications is defined as any adverse events that required additional pharmacological, interventional, or surgical management within 30 days after surgery. All postoperative complications were graded according to the Clavien-Dindo classification [23]. SSI is defined according to the criteria of the Centers for Disease Control and Prevention [24]. We divided SSI into superficial, deep incisional, and organ/space-related types occurring within 30 days after surgery. We will evaluate postoperative pain on postoperative days 1, 2, and 3 using a numeral rating scale. The verbal numeral rating scale ranged from 0 to 10 (0 = no pain and 10 = worst pain). To analyze the quality of life, the SF-36 and body image questionnaire will be used and documented by the patient 12 months postoperatively (Fig. 2). All outcomes will be evaluated by the investigators and they are specially trained for reliability.

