## Discussion

This is the first randomized controlled trial to compare absorbable barbed sutures with absorbable monofilament sutures for midline fascia closure in minimally invasive surgery for colorectal and gastric cancers.

The current guidelines recommend monofilament suture material for continuous closure of the midline incision [22]. However, absorbable monofilaments can stretch up to 30% of their length and slip easily, loosening the suture material [15]. At the end of the monofilament suture, it is necessary to create a surgical knot that can break and cause an incisional hernia. Barbed sutures were introduced several years ago. This novel suture material has a self-anchorage system that maintains tension and requires no surgical knots after the sutures are strained [25]. Although barbed sutures have been applied in uterine closure, arthroscopic surgery, and gastrointestinal surgery, they are not widely used for fascia closure due to the lack of evidence of its safety and efficacy.

In this trial, we aimed to determine which suture material is safer for patients who require mini-laparotomy in minimally invasive surgery. The strength of this study was its prospective and randomized design. If absorbable barbed sutures demonstrate comparable results to those of monofilament sutures, they might be suggested as an alternative suture material for abdominal fascia closure.

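### Safety is a stated aim of a 3-year trial, but closure-related events after day 30 and the consequences of hernia have no stated collection

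*Protocol article*

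**What the plan says.** The protocol article makes safety an aim in two places. Objective {7}: "This study aimed to evaluate the safety and efficacy of absorbable barbed sutures for midline fascia closure in minimally invasive surgery". Discussion: "In this trial, we aimed to determine which suture material is safer for patients who require mini-laparotomy in minimally invasive surgery". The Introduction gives insufficient evidence on safety and efficacy as the reason barbed sutures have not been adopted clinically for fascial closure.

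Harms are then bounded at day 30. The harms section {22} states: "Any adverse events that required additional pharmacological, interventional, or surgical management within 30 days after surgery will be collected and monitored". The next sentence ties this to the secondary outcome: "We regarded adverse events as postoperative complications and graded according to the Clavien-Dindo classification". Under Secondary outcomes the definition is the same: "Postoperative complications is defined as any adverse events that required additional pharmacological, interventional, or surgical management within 30 days after surgery". All three types of surgical site infection have the same limit, and pain is rated on postoperative days 1, 2 and 3 only.

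Follow-up is much longer. Study design {8}: "The investigator will examine the patients until discharge and at 6, 12, 18, 24, and 36 months postoperatively". At those five visits incisional hernia is sought by physical examination and computed tomography (Primary outcome). SF-36 and a body image questionnaire are completed once, at 12 months.

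**The concern.** The aim and the collection rule do not match. The article is not silent on the window, so this is not a detail left to a fuller document. It states a limit, in both the outcome section and the harms section, and it equates adverse events with the 30-day complications, so no second and longer safety record is described.

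If the arms differ after day 30 in late wound infection or sinus, suture removal or re-intervention at the midline wound, the planned comparison will not show it. Hernias are counted, but a small defect seen only on a scan counts the same as one that incarcerates or needs repair. The Discussion would suggest barbed suture as an alternative if results are comparable. A reader would take that to cover late tolerability of the closure, which the described data do not address beyond hernia occurrence and one quality-of-life assessment.

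**Working it through.** **1. The plan's own figure.** The only calculated figure is the sample size, which is driven by hernia: 15% v 5% at 3 years, two-sided α 0.05, power 80% (Sample size {14}). With mean proportion 0.10:

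n = [1.960 × √(2 × 0.10 × 0.90) + 0.842 × √(0.15 × 0.85 + 0.05 × 0.95)]² / 0.10² = (0.8315 + 0.3521)² / 0.01 = 140.1, so 141 per group.

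This reproduces the stated 141. The point here concerns what is collected and leaves that number alone.

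**2. What is collected, and until when.**

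| Measure | Window stated | Section |
|---|---|---|
| Adverse events needing added management | to day 30 | Adverse event reporting and harms {22} |
| Postoperative complications, graded | to day 30 | Secondary outcomes |
| Surgical site infection, all types | to day 30 | Secondary outcomes |
| Pain score | days 1, 2, 3 | Secondary outcomes |
| SF-36 and body image | once, month 12 | Secondary outcomes |
| Incisional hernia occurrence | months 6, 12, 18, 24, 36 | Primary outcome |

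**3. Visits against the window.** The earliest post-discharge visit is at month 6. None of the five scheduled visits (0 of 5) falls inside the 30-day window, and all five already include an examination for hernia.

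**4. Sorting late events by whether a row above captures them.**
- Hernia present or absent: captured to month 36.
- General late burden felt by the patient: captured once, at month 12, without identifying a wound or suture event as the cause.
- Late wound infection or sinus, suture removal, re-intervention at the midline wound: no row.
- Hernia symptoms, incarceration or repair: no row; only the hernia itself is recorded.

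**5. What added data could show.** The documents give no late event rates, so the rates here are assumptions. The test is the two-sided comparison of two proportions with 312 / 2 = 156 per arm, and power = Φ{[d − 1.960 × √(2p̄(1 − p̄)/156)] / √[(p₁(1 − p₁) + p₂(1 − p₂))/156]}, where d is the difference and p̄ the mean proportion.

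| Assumed late rates | Power |
|---|---|
| 1% v 3% | 24% |
| 2% v 5% | 30% |
| 3% v 6% | 25% |
| 5% v 10% | 39% |

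If no event of a given type occurred in an arm, the one-sided 95% upper bound would be 1 − 0.05^(1/156) = 1.9%, or 2.1% with 141 followed. Late events should therefore be reported as counts and not tested as a hypothesis. Even so, a bound near 2% is information that the trial would otherwise lack.

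**The case against.** The strongest reply is that hernia is the main late harm of a midline closure and the trial counts it for the full 3 years. That stands. A reader might infer that late hernia harms go uncounted; the Primary outcome section contradicts this, and only the consequences of hernia lack a stated collection.

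A reader might also infer that the trial cannot say which suture is safer. That is too strong: it can compare graded 30-day complications, surgical site infection, early pain, 12-month quality of life and 3-year hernia occurrence.

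Nor does a safety statement rest on about 3% of follow-up. Thirty days out of about 1,096 is 2.7%, but that is a share of calendar days and not of expected harm, and it ignores the hernia and quality-of-life data. Any count of missed patients would rest on invented rates.

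Two further objections have some force. A 30-day window is a defined and gradable choice, and there is no reason to abandon it for early complications. The participant timeline figure and the full protocol are not available here, so one cannot assert that nothing else is noted at the later visits. What can be said is that the text as written limits adverse events and complications to day 30 and provides no other place in the arm comparison for late wound and suture events.

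**Conclusion.** The point holds in a limited form. As described, the safety comparison consists of 30-day complications and infections, early pain, hernia occurrence to 3 years and quality of life at 12 months. That is narrower than the aim in the Objective and Discussion. The missing parts are closure-related wound and suture events after day 30 and the clinical consequences of hernia.

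The size cannot be given in patients or percentage points. The gap is one of scope: it touches a stated objective, not the primary analysis or the sample size. The conclusion assumes that the article's text governs collection and that the unseen timeline figure adds no later harms record. If that figure or the full protocol does provide one, the remedy reduces to correcting the article's two 30-day statements.

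**What to change.** Keep the 30-day complication and surgical site infection outcomes as they are. In Secondary outcomes and in Adverse event reporting and harms {22}, add a descriptive secondary safety outcome: closure-related events from day 31 to month 36, recorded at the existing 6, 12, 18, 24 and 36 month visits and reported as counts by arm. List the events: wound infection or sinus, suture removal, re-intervention at the midline wound, and hernia symptoms, incarceration or repair. Count bowel obstruction only when it is attributed to the midline closure or a hernia, because these patients are under surveillance for cancer recurrence and obstruction may have other causes.

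If this is not adopted, limit the safety wording in the Objective and Discussion to what is measured.

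The cost is one short form page at visits that already take place, and an amendment by the route the article already describes. No visit, scan or patient is added. The downside is slightly more data entry and some weaker data: recruitment began in December 2021, so events at visits already past would be taken from records in retrospect, by investigators who know the allocation. The report should say so and show which events were collected that way.

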### Frequency and plans for auditing trial conduct {23}

The study data will be maintained in accordance with Good Clinical Practice requirements by the investigators. The original study data and information will be securely stored for a minimum of 5 years following the completion of the study. Data monitoring reports will be submitted to the ethics committee every 3 months.

### Plans for communicating important protocol amendments to relevant parties (e.g., trial participants, ethical committees) {25}

If the protocol needs to be modified, it will be reviewed again by the ethics committee, and, upon approval, the trial registry and protocol will be updated.

### Dissemination {31a}

The findings will be published in peer-reviewed journals and disseminated through scientific and academic conferences.

## Discussion

This is the first randomized controlled trial to compare absorbable barbed sutures with absorbable monofilament sutures for midline fascia closure in minimally invasive surgery for colorectal and gastric cancers.

The current guidelines recommend monofilament suture material for continuous closure of the midline incision [22]. However, absorbable monofilaments can stretch up to 30% of their length and slip easily, loosening the suture material [15]. At the end of the monofilament suture, it is necessary to create a surgical knot that can break and cause an incisional hernia. Barbed sutures were introduced several years ago. This novel suture material has a self-anchorage system that maintains tension and requires no surgical knots after the sutures are strained [25]. Although barbed sutures have been applied in uterine closure, arthroscopic surgery, and gastrointestinal surgery, they are not widely used for fascia closure due to the lack of evidence of its safety and efficacy.

In this trial, we aimed to determine which suture material is safer for patients who require mini-laparotomy in minimally invasive surgery. The strength of this study was its prospective and randomized design. If absorbable barbed sutures demonstrate comparable results to those of monofilament sutures, they might be suggested as an alternative suture material for abdominal fascia closure.

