**Discussion:**

This is the first randomized controlled trial to compare absorbable barbed sutures with monofilament sutures for midline fascia closure in minimally invasive surgery. If absorbable barbed sutures demonstrate superior results to those of monofilament sutures, this type of suture material may be recommended as an alternative option for abdominal fascia closure.

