### Sample size {14}

We mainly have used absorbable monofilament sutures for fascia closure, and the overall incidence of incisional hernia was about 15%. Barbed suture began to be used for fascial closure in August 2020 during colorectal surgery. Before this randomized controlled trial, we conducted a pilot study of barbed suture for fascia closure. A total of 60 patients underwent fascia closure with barbed suture during laparoscopic colorectal surgery, and incisional hernia occurred in 2 patients (3.3%) within 1 year after surgery. Assuming additional patients with an incisional hernia during follow-up period, we determined possible incisional hernia rate to 5% in the barbed suture group for 3 years after surgery. Therefore, we hypothesized that the incidence of incisional hernia at 3 years after surgery will be lower in the barbed suture group than in the monofilament suture group. The sample size was calculated on the basis of this analysis plan, assuming that the incisional hernia rate of the barbed suture and monofilament groups at 3 years after surgery will be 5% and 15%, respectively. We calculated that 141 patients per group needed to achieve a two-sided α of 0.05 and statistical power of 80% using a chi-squared test. Assuming a 10% dropout rate, it is necessary to recruit 312 patients. Finally, 156 patients were assigned to the barbed suture and monofilament groups. The calculations were performed using G*Power 3.1.

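### The main Discussion lets comparable results support barbed sutures, while the Abstract requires superior results and the design tests only superiority, with no margin

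*Protocol article*

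**What the plan says.** The article states two conditions for nearly the same recommendation.

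- Abstract, Discussion paragraph: the condition is "If absorbable barbed sutures demonstrate superior results to those of monofilament sutures".
- Main text, Discussion, last paragraph: "If absorbable barbed sutures demonstrate comparable results to those of monofilament sutures, they might be suggested as an alternative suture material".

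The operative sections agree with the Abstract.

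- Study design {8}: "The Barbed trial is a prospective, superiority, single-center, randomized trial".
- Sample size {14}, hypothesis: "the incidence of incisional hernia at 3 years after surgery will be lower in the barbed suture group than in the monofilament suture group".
- Sample size {14}, calculation: it assumes that "the incisional hernia rate of the barbed suture and monofilament groups at 3 years after surgery will be 5% and 15%, respectively" and concludes that "141 patients per group needed to achieve a two-sided α of 0.05 and statistical power of 80% using a chi-squared test".
- Statistical methods {20a}: chi-squared and Kaplan-Meier analyses of the primary outcome, judged at p < 0.05.

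The article gives no non-inferiority or equivalence margin, no confidence-interval rule, and no definition of what would count as comparable.

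**The concern.** Superiority and comparability are different conclusions and need different evidence. A superiority test can support the first. The second needs a limit on how much worse the new suture may be, and data precise enough to exclude anything beyond it. The article provides only the first kind of test, yet its closing statement on interpretation names the second kind of result.

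With only difference tests planned, the easiest way to apply the Discussion sentence is to treat p ≥ 0.05 as comparability. The same Discussion says that barbed sutures are little used for fascia because evidence on safety and efficacy is lacking. A null result read this way would seem to fill that gap without excluding a material excess of hernias. Having two criteria on record also leaves room to choose between them once the data are known.

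**Working it through.** **Inputs.** From Sample size {14}: 15% hernia with monofilament, 5% with barbed, two-sided α 0.05, 80% power, chi-squared test, 141 evaluable per arm. Assumed for illustration, because the article gives no such figures: true barbed rates of 15%, 20% and 22%, and the margins in step 5.

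**1. Reproduce the stated size.** Two proportions, pooled variance under the null, no continuity correction:

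n = [1.960·√(2·0.10·0.90) + 0.842·√(0.15·0.85 + 0.05·0.95)]² / 0.10² = 140.1, rounded up to 141 per arm.

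This matches the article, so the trial is sized as a superiority trial for a 10-point reduction.

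**2. Precision of a null result.** With a true rate of 15% in both arms:

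half-width = 1.96·√(2·0.15·0.85/141) = 0.083, or ±8.3 points.

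With all 156 randomised patients per arm evaluable it is 1.96·√(2·0.15·0.85/156) = 0.079. At 10% in both arms and 141 per arm it is 0.070. An observed difference of exactly zero, at 15% in each arm, would therefore still allow an excess of about 8 points on a base of 15%.

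**3. How often a worse suture gives a non-significant test.** The uncorrected chi-squared test was evaluated by exact enumeration: sum Bin(x; 141, p_mono)·Bin(y; 141, p_barbed) over all pairs with |Z| < 1.96, where Z = (y − x)/141 ÷ √(2·p̄(1 − p̄)/141) and p̄ = (x + y)/282.

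| True barbed vs monofilament | Non-significant | Significant, favouring monofilament |
|---|---|---|
| 20% vs 15% | 80.3% | 19.6% |
| 22% vs 15% | 67.2% | 32.8% |

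The normal approximation gives 80.4% and 67.3% for the non-significant column.

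**4. How many of those would look comparable.** Non-significant trials with an observed barbed excess above 5 points make up 27.5% of all trials at 20% vs 15%, and 31.5% at 22% vs 15%. That leaves about 53% and 36% of all trials with a non-significant result and an observed excess of 5 points or less. The 80% and 67% are therefore upper bounds on how often a misleading conclusion might be drawn.

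**5. What a comparability claim would need.** Equal true rates of 15%, one-sided α 0.025, 80% power, assumed margin m:

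n = (1.960 + 0.842)²·2·0.15·0.85 / m²; power at 141 = Φ(m/√(2·0.15·0.85/141) − 1.960).

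| Assumed margin | n per arm | Power at 141 per arm |
|---|---|---|
| 5 points | 801 | 22% |
| 7.5 points | 356 | 42% |
| 10 points | 201 | 65% |

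If both true rates were 10%, the sizes would be 566, 252 and 142 and the power 29%, 56% and 80%. Only there, with a margin as large as the event rate itself, does the planned size come close to sufficient.

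**The case against.** The strongest case on the other side is that this is one hedged sentence in narrative prose. It says that barbed sutures might be suggested. It sets no p-value rule and does not say which results must be comparable. The design, hypothesis, sample size and primary test agree with each other, and the sentence changes none of them. This stands, and it limits the severity: the analysis is as valid with the sentence as without it.

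Two stronger readings are tempting, and the article supports neither.

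- A reader might infer that the investigators plan to treat a non-significant test as equivalence. The article nowhere says so. The wording permits that reading because comparable is undefined and only difference tests are planned, but it does not state it.
- A reader might infer that the trial can hardly fail, since significant and non-significant results would both favour the new suture. This overlooks the other tail of the two-sided test. A result significantly favouring monofilament meets neither criterion, and step 3 puts it at about 20% and 33% of trials in the two scenarios.

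The 20% and 22% rates are assumptions, and the only barbed-suture data in the article point the other way: 2 hernias in 60 pilot patients (3.3%) within 1 year. That pilot was small and uncontrolled and had shorter follow-up than the 3-year endpoint, so it does not settle what a null result would mean. The non-inferiority sizes rest on assumed margins for a design the trial does not claim. They show how far the planned size is from such a claim, and reveal no error in the stated calculation.

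The conflict between the two criteria remains. It lies within the article itself, so it is not a detail left to an analysis plan that is not shown.

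**Conclusion.** The point holds as an inconsistency about what the trial may conclude, and it should be fixed. The Abstract and the main Discussion set different conditions for nearly the same recommendation, and only the Abstract's condition fits the superiority design. At the planned size a null result cannot establish comparability: at the protocol's own 15% rate in both arms the interval is about ±8.3 points, and a suture truly 5 or 7 points worse would escape significance in about 80% or 67% of trials. The interval assumes 141 evaluable patients per arm and a true 15% rate in both. The percentages also assume the uncorrected chi-squared test and the illustrative barbed rates. The primary analysis itself is not affected.

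**What to change.** Rewrite the last sentence of the main Discussion to match the Abstract: barbed sutures will be suggested on efficacy grounds only if superiority on the primary outcome is shown. Add that a non-significant result is inconclusive and will be reported as the risk difference with its 95% confidence interval, and not described as comparability.

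The cost is about one sentence, with no change to sample size, procedures, data collection or the primary test. The analysis is planned only after every patient has completed 3-year follow-up, so the change can be made beforehand through the amendment route in section {25}. The sponsor gives up only a claim that the design cannot support. Keeping a comparability claim instead would need a justified margin, a confidence-interval rule and a matching sample size. Step 5 shows that at a 15% rate this would mean a larger trial for every margin listed.
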